### Study population

The study population will consist of 100 postmenopausal women aged 45 to 70 years with a BMD T-Score between 0.0 and -2.49. In- and exclusion criteria are detailed in Table 1. Given the possible administration of placebo treatment, women with osteoporosis are excluded from the study for ethical reasons. Study participants are being recruited through advertisements in local newspapers; recruitment has started in January 2007.

**Table 1 T1:** In- and exclusion criteria

**Inclusion criteria**
• Women aged 45 to70 years
• Natural or surgical menopause = 1 year
• T-Score between 0.0 and -2.49 (spine or proximal femur – total or femoral neck, measured by DXA)

**Exclusion criteria**

• Osteoporosis (T-score = -2.5 in spine or proximal femur – total or femoral neck, measured by DXA)
• Severe vertebral fracture, as identified by screening DXA assessment
• Any history of metabolic disease that could affect bone metabolism: hyperparathyroidism, osteogenesis imperfecta, Paget's disease, osteomalacia
• Thyroid disease (if receiving thyroid hormone replacement, the patients must be euthyroid and on a stable dose of thyroid hormone)
• Impaired renal function (estimated creatinine clearance <30 ml/min)
• History of previous or active malignancy of any organ system, treated or untreated, within the past 5 years.
• History of corticosteroid treatments during 6 months or more, daily dosage >5 mg
• BMI < 18 or >30 kg/m^2^
• Treatments with estrogens, SERMs, tibolone, calcitonin, strontium ranelate, teriparatide or PTH, or oral bisphosphonates in the previous year, if duration > 2 weeks. Treatment with iv bisphosphonates or iv calcitonin of any duration in the previous year

### Study medication

Participants receive 200 IU calcitonin nasal spray once daily or the matching placebo spray, provided by Novartis Pharmaceuticals, Basel, Switzerland. All patients fulfilling the inclusion/exclusion criteria will be given study medication. Odds of receiving active treatment or placebo are 1:1. Medication labels comply with the legal requirements in Switzerland and will be printed in the local language. The storage conditions for the study drug as well as the randomization number are specified on the medication label. No patient identifier is stated on the label.

All patients receive a calcium and vitamin D supplement (1000 mg/880 UI per day). If the supplement is not tolerated, the dose will be reduced or, if necessary, the supplement will be stopped. In this case, the participant may continue the trial and will be given advice on adequate dietary calcium intake. A vitamin D supplement of 800 IU/day will then be prescribed during the winter months.

Drug accountability will be noted during visits and at the completion of the trial. Patients will be asked to return all unused medication at the end of the study.

### Blinding

Patients, investigator staff, persons performing the assessments, and data analysts will remain blind to the identity of the treatment from the time of randomization until database lock. The identity of the treatments will be concealed by the use of study drugs that are all identical in packaging, labeling, schedule of administration, appearance, taste, and odor. Randomization data are kept strictly confidential until the time of unblinding and will not be accessible by anyone else involved in the study. Unblinding will only occur in the case of patient emergencies and at the conclusion of the study.

### Study procedures

Potential participants will undergo a screening procedure, including recording of medical history, physical examination, blood sampling, and BMD measurements and vertebral fracture assessment (VFA) by DXA (Prodigy, GE Healthcare Technologies, Waltham, Wisconsin, USA). Participants fulfilling the inclusion/exclusion criteria at screening will be included in the study. During the study, visits to the trial center will take place every 6 months (Table 2).

**Table 2 T2:** Visit schedule

	Visit 1	Visit 2	Visit 3	Visit 4	Visit 5	Visit 6
Period	Screening	Baseline	Month 6	Month 12	Month 18	Month 24

Day	-7 to -3	0	180 ± 14	360 ± 14	540 ± 14	720 ± 14

Informed consent	X					
In-/exclusion criteria	X	X				
Medical history	X	X				
Prior/Concomitant medication	X	X	X	X	X	X
Vital signs		X		X		X
Physical examination	X					X
Adverse events			X	X	X	X
DXA	X			X		X
pQCT		X		X		X
Laboratory test	X			X		X
Bone markers	X	X	X	X	X	X
Antibody test						X
Study drug dispensing		X	X	X	X	
Drug accountability			X	X	X	X
Study termination sheet						X

### Efficacy assessments

#### Bone microarchictecture measurements

Bone microarchitecture will be investigated by p-QCT at baseline and after one and two years. Three-dimensional high-resolution measurements will be performed at the distal radius and tibia using an Xtreme CT device (Scanco Medical AG, Bassersdorf, Switzerland), as described by others [15]. In brief, the non-dominant limb (or the nonfractured limb in case of prior fractures) will be scanned at the standardized locations for human in vivo measurements. The following settings are used: effective energy of 60 kVp, matrix size 1536 × 1536, x-ray tube current 900 μA, slice increment 82 μm. One hundred and ten slices will be obtained with a voxel size of 82 μm. The effective dose for one Xtreme CT standard measurement is 3 μSv per site. Processing of the obtained scans will be done in accordance with the default protocol of the device. Table 3 lists the assessed bone parameters. In our institution, the in-vivo coefficient of variation (CV%) for these bone indices ranges from 0.5 – 1% (vol. densities) to 3 – 5% (TbN). Quality control is performed on a daily basis.

**Table 3 T3:** Parameters of bone microarchitecture

**Bone densities**
• cortical bone density (Dcort; mgHA/cm^3^)
• trabecular bone density (Dtrab; mgHA/cm^3^)
• meta trabecular bone density (Dmeta; mgHA/cm^3^)
• inner trabecular bone density (Dinn; mgHA/cm^3^)
• average bone density (Dtot; mgHA/cm^3^)

**Bone structure**

• trabecular bone volume to tissue volume (BV/TV; %)
• number of trabeculae (Tb.N; mm^-1^)
• trabecular thickness (Tb.Th; *μ*m)
• trabecular separation (Tb. Sp; *μ*m)
• cortical thickness (C.Th; *μ*m)
• index of the inhomogeneity of the network (Tb.1/N.SD)
• cross-sectional area (CSA; mm^2^)

#### Bone mineral density measurements

Spine and hip bone mineral density will be measured at the baseline visit and after one and two years by DXA (Prodigy, GE Healthcare Technologies, Wisconsin, USA). The irradiation dose is 7 μSv per examination.

#### Laboratory test

Fasting serum samples will be obtained from all patients at the 6-monthly visits. Serum will be stored at -70°C to allow analysis in batches. Serum total procollagen type 1 amino-terminal propeptide (P1NP), a marker of bone formation, and serum C-terminal telopeptide of type I collagen (β-crosslaps, CTX), a marker of bone resorption, will both be measured using electrochemiluminescence immunoassays (Elecsys 2010, Roche Diagnostics). The intrassay coefficients of variation (CV%) for these measurements are 2.3–3.7% and 1.6–4.7%, respectively. Levels of serum PTH (7–84) will also be assessed using an electrochemiluminescence immunoassay (CV 4.3–7.1%); serum 25-hydroxyvitamin D will be determined by a competitive immunoassay (ELISA; CV 5.3–6.7%).

Serum and urine biochemistry as well as hematology will be measured immediately after blood sampling in the routine laboratory according to standard procedures. The titer of calcitonin antibodies will be assessed at end of the study.

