## Background

Osteoporosis is characterized by compromised bone strength and higher fragility, resulting in an increased fracture risk [1]. The measurement of areal bone mineral density (BMD) by dual-energy X-ray absorptiometry (DXA) is the most common way to measure bone mass and to assess fracture risk. Yet, bone strength is also determined by bone geometry, bone microarchitecture, bone remodelling and intrinsic tissue quality [2]. Thus, it is not surprising that BMD only partially explains the variance of strength and fracture risk [3]. It has been postulated that markers of bone remodelling determined in blood or urine could be independent predictors of fracture risk [4]. Assessment of changes in bone microarchitecture has been limited, since bone biopsies were necessary to investigate these parameters in the past. This technique is limited to a non-weight bearing bone such as the iliac crest. Today, high-resolution peripheral quantitative computerized tomography (p-QCT) allows an efficient and quantitative evaluation of bone microarchitecture [5,6]. It determines in three dimensions true volumetric density (g/cm^3^), and can directly assess trabecular thicknesses, trabecular separations, and trabecular number, and also provides additional geometric variables such as cross-sectional area (CSA) and information on structural pattern (rod vs. plate structure) with a relatively low irradiation, high accuracy and precision [7]. P-QCT thus provides a unique non-invasive opportunity to explore the effects of diseases on bone microarchitecture and of therapies intended to halt or reverse these changes [8].

Postmenopausal bone loss and fracture risk are associated with an imbalance in bone turnover. As a therapeutic agent, calcitonin binds to specific receptors on the osteoclasts and reduces their relative hyperactivity.

The formula of nasal calcitonin is well tolerated. The most common side effects consist of mild or moderate rhinitis symptoms, such as nasal congestion and sneezing, or nasal dryness [9,10]. Rarely, hypersensitivity reactions may occur.

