### Statistical methods

#### Sample size calculation

A total number of 80 patients (40 in the calcitonin group and 40 in the control group) is necessary to have a statistical power of 80% to detect an expected difference of 3.5% in BV/TV [13]. Due to an expected drop-out rate of 20%, a total of 100 patients should be enrolled.

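### A single calcitonin-antibody titre at month 24 leaves women not seen at that visit without a result and gives no pre-dose reference (low severity)

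*Protocol article*

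**What the plan says.** All references are to the protocol article.

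- **Laboratory test:** "The titer of calcitonin antibodies will be assessed at end of the study". The same section has fasting serum taken from every participant at the 6-monthly visits and adds: "Serum will be stored at -70°C to allow analysis in batches".
- **Study procedures, Table 2:** the row "Antibody test" has one mark, under Visit 6 (month 24, day 720 ± 14). Screening, baseline and months 6, 12 and 18 are blank. Bone markers are marked at all six visits. No early-withdrawal visit is shown.
- **Sample size calculation:** "Due to an expected drop-out rate of 20%, a total of 100 patients should be enrolled".
- **Table 1, exclusion criteria:** prior calcitonin excludes a woman only if used in the previous year. For non-intravenous use it must also have lasted more than 2 weeks; intravenous use counts at any duration. Older use, or brief recent non-intravenous use, is therefore allowed.
- **Background:** "Rarely, hypersensitivity reactions may occur". The article does not link these reactions to the antibody titre.

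**The concern.** The text and Table 2 agree, so this is a stated design choice and not a slip. It has two consequences.

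First, the result depends on attendance at month 24. The plan itself expects a fifth of the women to drop out, so the titre would describe the women still present at two years and not all who were dosed.

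Second, there is no pre-dose value. Because some earlier calcitonin users may enter, a positive titre at month 24 could predate the trial. The placebo arm gives a background rate for the group but cannot settle the question for one woman.

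What is at stake is how far the antibody finding can be interpreted. The efficacy conclusions are not at stake.

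**Working it through.** **Inputs.** 80 women needed, 40 per arm; 20% drop-out; 100 enrolled (Sample size calculation). Allocation is 1:1 (Study medication), so 50 per arm. Equal drop-out in the two arms is an assumption.

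**Reproducing the plan's figure.** 80 / (1 − 0.20) = 100, which matches the stated enrolment.

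**Titres missing as scheduled.** 0.20 × 100 = 20 women, and 0.20 × 50 = 10 on calcitonin. This is an upper figure in so far as some women who leave or stop treatment may still be seen at month 24. Pre-dose titres available: 0 of 100.

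**What 10 missing results do to the calcitonin-arm proportion.** If x of 40 observed women are positive, the proportion among all 50 lies between x/50 (no missing woman positive) and (x + 10)/50 (all positive). The values of x are assumed, since the article gives no antibody rate.

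| Positive among 40 observed | Lowest, of 50 | Highest, of 50 |
|---|---|---|
| 4 (10%) | 4/50 = 8% | 14/50 = 28% |
| 12 (30%) | 12/50 = 24% | 22/50 = 44% |
| 20 (50%) | 20/50 = 40% | 30/50 = 60% |

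The width is 10/50 = 20 percentage points in every row, whatever the reason for leaving.

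**What stored serum could recover.** Assume a constant drop-out hazard with 20% lost by month 24: h = −ln(0.8)/24 = 0.0093 per month. Loss by month 6 is 1 − exp(−6h) = 5.4%, or about 5 of 100 women. The other 20 − 5 = 15 or so would have at least one on-treatment sample. On calcitonin, about 0.054 × 50 = 2.7 women would still lack one, so the width falls from 20 to about 2.7/50 = 5.4 points. The drop-outs' titres would then reflect a shorter exposure than month 24.

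**Is baseline serum available?** The storage sentence does not name the baseline visit. Table 2 marks bone markers at screening and baseline, and these markers are to be assayed from stored serum. Baseline storage is therefore a direct inference, but it is not stated. Spare volume is not documented.

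**The case against.** **The titre is peripheral.** It is neither the primary nor the secondary endpoint, and the article states no immunogenicity objective or analysis. This stands and sets the severity. Timing antibody onset against the bone response would be an added objective, and its absence is not a fault.

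**The end of the study might mean each woman's own end.** The study termination sheet also appears only under Visit 6, although it would be needed for early leavers, and a condensed article may leave withdrawal procedures to the full protocol. This is a fair reading, but the column is labelled month 24 and nothing shown says otherwise. Even if it is right, the missing pre-dose titre remains.

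**Stronger readings that the documents do not support.**

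- A reader might infer that titres will exist only for women who tolerated two years of spray. Stopping the spray is not the same as missing month 24, and nothing says that women who stop treatment are not seen then.
- A reader might infer that the antibody rate is biased downward. Antibody-positive women might leave more often, but early leavers also have shorter exposure and so perhaps fewer antibodies. The direction is unknown.
- A reader might infer that hypersensitivity goes unseen. Adverse events are recorded throughout and analysed in all randomized women who took at least one dose, including those who drop out.

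**The pre-dose gap may be small.** The number of prior calcitonin users is not given and could be near zero, and the randomized placebo arm supplies the group-level background. This stands; only attribution in an individual woman is affected.

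**Conclusion.** The point holds as a minor weakness of the schedule. As written, women not seen at month 24 have no titre, and no positive titre can be shown to be treatment-emergent in an individual. The size is up to about 20 of 100 women without a result and up to 20 percentage points of uncertainty in the calcitonin-arm proportion. This rests on the plan's 20% drop-out, on equal drop-out by arm, and on drop-outs not attending Visit 6. No direction of bias can be claimed. Sample size, the primary and secondary endpoints and adverse-event capture are untouched. Severity is low; the case for change is that most of the gap can be closed cheaply.

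**What to change.** In the Laboratory test section and Table 2:

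1. Define the antibody sample as the month-24 sample or, for a woman who leaves early, her last stored on-treatment sample.
2. Assay the stored baseline sample in the same batch, at least for every woman with a positive on-treatment titre.
3. Report treatment-emergent positivity by arm, with the number of women lacking an on-treatment titre. Release titres only after database lock, in line with the Blinding section, because a positive result may suggest the allocation.

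**Cost.** About 15 extra on-treatment assays for early leavers (constant hazard assumed), plus one baseline assay per positive woman, or about 100 if all are tested. No new visit or blood draw is needed, provided that enough serum is stored; baseline storage should be confirmed first. About 5 women who leave before month 6 would still have no on-treatment titre.

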### Safety assessments

Safety assessments will include the monitoring and recording of all adverse events (AEs), including serious adverse events (SAEs), the regular monitoring of hematology, blood chemistry and urine values, regular monitoring of vital signs, physical condition and body weight. Body height will be measured 6-monthly with a Harpeden stadiometer (Holtain Ltd, Crymych, UK).

### Data management

All original data will be recorded in the patient's source documentation. Subsequently, anonymized data will be entered into an electronic database and displayed in the patient data listings. Tables will display counts of missing values. Quality control of the data will be done at regular intervals, using descriptive statistics and visual analyses to check for inconsistencies and extreme values. Detected errors will be rectified according to the source data. Data will be handled in accordance with the good clincal practice guidelines and applicable local regulations. Data management and analysis as well as interpretation and publication of the results remain under the responsibility of the principal investigator and will be performed by the study team of the University Hospitals of Geneva.

### Statistical methods

#### Sample size calculation

A total number of 80 patients (40 in the calcitonin group and 40 in the control group) is necessary to have a statistical power of 80% to detect an expected difference of 3.5% in BV/TV [13]. Due to an expected drop-out rate of 20%, a total of 100 patients should be enrolled.

#### Statistical analysis

Data will be summarized with respect to demographic and baseline characteristics, efficacy observations and measurements, and safety observations and measurements.

To assess the treatment effects of calcitonin on bone microarchitecture and provide a proof of concept, the primary analysis of the efficacy endpoints in this exploratory trial will be based on the observed data of the per-protocol population. Secondarily, an ITT analysis may be performed to test the robustness of the results.

For each analyzed parameter a two-sided t-test will be applied. The change from baseline between the two different groups (active treatment/placebo) will be compared by an analysis of covariance (ANCOVA) model with change as the response variable, the baseline value as a covariate, and treatment as a fixed factor.

The assessment of safety will be based mainly on the frequency of adverse events and on the number of laboratory values that fall outside of pre-determined ranges. Other safety data (e.g. electrocardiogram, vital signs, special tests) will be considered as appropriate.

Analysis of adverse events will be based on the safety population which includes all randomized patients who have taken at least one dose of the study drug. Adverse events will be summarized by presenting, for each treatment group, the number and percentage of patients having any adverse event, having an adverse event in each body system and having each individual adverse event. Any other information collected (e.g. severity or relatedness to study medication) will be listed as appropriate.

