Prolonged administration of intranasal calcitonin can prevent postmenopausal bone loss and is also able to increase trabecular bone mass among patients presenting established osteoporosis [10,11]. It has been demonstrated that the prolonged daily administration of 200 IU intranasal calcitonin inhibits bone resorption, increases lumbar spine BMD by 1.7%–3.3% after one year, and reduces vertebral fracture risk [9,12]. Furthermore, specific modification of bone microstructure was demonstrated at the distal radius using magnetic resonance imaging [13].

A possible effect of calcitonin on bone microarchitecture could be investigated using high-resolution p-QCT. By assessing structural bone changes, the present study should thus provide new insights in the mode of action of nasal calcitonin. We hypothezise that - compared to placebo - calcitonin improves or maintains microstructural parameters, with a possible difference between weight bearing and non-weight bearing bones.

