## Methods

### Study design

This is a monocentric, randomized, placebo-controlled, double-blind trial over two years, assessing the effects of nasal calcitonin (200 IU/day) on bone microarchitecture measured by high resolution p-QCT in postmenopausal women.

This protocol was initiated by the principal investigator and has been accepted by the ethics committee of the University Hospitals of Geneva and by the Swiss legislative authority (Swissmedic). It has been registered in a public clinical trial data base [ClinicalTrials.gov number NCT00372099] [14].

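### The primary efficacy analysis rests on observed per-protocol data and ITT is only optional, so the comparison with placebo may be reported without any check that keeps the randomised groups intact

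*Protocol article*

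**What the plan says.** The design is described under Study design: "This is a monocentric, randomized, placebo-controlled, double-blind trial over two years". The Statistical analysis section gives the purpose of the efficacy analysis as follows: "To assess the treatment effects of calcitonin on bone microarchitecture and provide a proof of concept". In the same sentence it fixes the population: "the primary analysis of the efficacy endpoints in this exploratory trial will be based on the observed data of the per-protocol population". The next sentence reads: "Secondarily, an ITT analysis may be performed to test the robustness of the results".

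The comparison is one of difference from placebo. The section says "For each analyzed parameter a two-sided t-test will be applied", describes an ANCOVA of change adjusted for baseline, and sets no non-inferiority margin. The Sample size calculation allows for attrition: "Due to an expected drop-out rate of 20%, a total of 100 patients should be enrolled". Only the adverse event analysis is tied to all randomised women who took at least one dose.

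**The concern.** Randomisation makes the two arms comparable as randomised. A per-protocol set is formed later, by who stayed and who kept to the protocol, and restricting to observed data adds a second filter of the same kind. If either filter works differently in the two arms, the difference between arms mixes the drug effect with the effect of selection.

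The protocol gives some reason to think that adherence could depend on treatment. On the drug it says: "The most common side effects consist of mild or moderate rhinitis symptoms, such as nasal congestion and sneezing, or nasal dryness". It gives no figure for withdrawal by arm.

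A single biased analysis matters less when an ITT result stands beside it. Here that result is optional, and the wording lets the choice be made after the per-protocol result is known. An investigator could follow the plan exactly and report only the per-protocol contrast.

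**Working it through.** **Inputs from the protocol.** 40 per arm, 80% power, a difference of 3.5% in BV/TV, 20% drop-out, 100 enrolled, 1:1 allocation, two-sided tests, and p-QCT at baseline, month 12 and month 24. **Assumed, because the article does not give them:** alpha 0.05, the SD, the pattern of selection, the correlation r between month-12 and month-24 change, and the number scanned at month 12.

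**1. The plan's own figure.** 80 / (1 − 0.20) = 100, which reproduces the stated enrolment. The expected loss is 100 − 80 = 20 women through drop-out. Exclusions for protocol deviations would add to this.

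**2. SD implied by the sample size.** The normal formula gives 3.5 / [(1.960 + 0.842) × √(2/40)] = 5.59. The noncentral t gives a standardised difference of 0.634, so SD = 3.5 / 0.634 = 5.52.

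**3. Bias from exclusion.** Let a share e of an arm be excluded, and let the excluded women differ from the retained women by k SDs. The retained mean then differs from the full-arm mean by −e × k × SD. The bias in calcitonin minus placebo is (−e_C × k_C + e_P × k_P) × SD. With SD 5.59:

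| e_C, e_P | k_C, k_P | Bias | Share of 3.5 | Two-sided type I error |
|---|---|---|---|---|
| 20%, 20% | −0.5, −0.5 | 0 | 0% | 5% |
| 20%, 20% | −0.5, 0 | +0.56 | 16% | 7.3% |
| 20%, 20% | 0, −0.5 | −0.56 | 16% | 7.3% |
| 20%, 20% | −0.5, +0.5 | +1.12 | 32% | 14.5% |
| 30%, 10% | −0.5, −0.5 | +0.56 | 16% | 7.3% |

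The first row matters as much as the others: equal selection in both arms gives no bias. The second and third rows show that the sign can go either way.

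**4. A near-worst case.** Suppose that exactly the worst 20% of one arm at month 12 leave and nobody in the other arm is selected. The remaining mean at month 24 shifts by (0.280 / 0.8) × r × 5.52 = 0.35 × r × 5.52. This is 0.58, 0.97 or 1.35 for r = 0.3, 0.5 or 0.7, or 17% to 39% of 3.5. If it dilutes the effect, power at 40 per arm is about 65%, 53% or 41% (66%, 55% or 44% if the smaller variance after truncation is allowed for). In the other direction, with no true effect, type I error is about 7%, 12% or 19%. This is an upper bound on concern, not a forecast.

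**5. Power under the alternative.** A longitudinal model that also uses month-12 scans has an approximate effective n per arm of 1 / [(1 − r²)/40 + r²/n12]. With n12 = 45 to 48, this is 41 to 44 for r = 0.5 to 0.7, and only about 40.5 for r = 0.3. With SD 5.52 and r = 0.5 to 0.7:

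- full effect of 3.5: power 81–83%;
- 10% dilution (0.9 × 3.5 = 3.15): 72–75%;
- 20% dilution (0.8 × 3.5 = 2.80): 62–65%.

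The 81–83% must not be set against the 41–65% in step 4, because one assumes no loss of effect and the other assumes harmful selection. An unbiased per-protocol analysis at 40 per arm has the planned 80%.

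**The case against.** The choice is deliberate and openly labelled. The trial is called exploratory, and its aim is to learn how the drug acts; for that, the effect in women who take it is a fair question. The hypothesis is modest: "calcitonin improves or maintains microstructural parameters". Participants, staff, assessors and data analysts stay blind until database lock, which limits selective exclusion. The Background also describes the nasal formulation as well tolerated. All of this stands, and it lowers the severity. It does not make the per-protocol groups comparable, because tolerability or response can drive exclusions without anyone knowing the allocation.

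Drop-out and per-protocol exclusion are also different things. A woman with no follow-up scan is missing under ITT as well, so changing the population does not recover her. That is correct, and it limits what the fix can deliver.

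A reader might go further and infer any of the following, which the document does not support:

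- *Women losing bone will leave after the month-12 DXA.* Nothing says that results are disclosed to participants or lead to withdrawal.
- *Women with only a month-12 scan contribute nothing.* The endpoint is change over two years with scans at both years, and the article does not fix the visit used in the ANCOVA.
- *The result will favour calcitonin, or power will fall to about half.* Both need an assumed pattern of selection, and the direction is unknown.

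The article does not define who belongs to the per-protocol set. That is commonly left to the full protocol or analysis plan and is not held against it here.

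**Conclusion.** The point holds in a limited form. The article itself fixes observed per-protocol data as primary and leaves ITT optional, so this is a stated rule and not a detail deferred to another document. Followed as written, it can produce a comparison with placebo that has no randomisation-based check, in a trial that expects to lose a fifth of its women. The direction of any bias is unknown and its size cannot be fixed from the document. The illustrations run from zero to about a third of the target difference, or somewhat more in the near-worst case, and all depend on an assumed alpha, a back-solved SD of about 5.5 and assumed selection. In an exploratory, blinded trial this should be fixed; it is not a reason to stop.

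**What to change.** **Minimum.** In the sentence on ITT, change *may* to *will*, and state that the result is reported beside the per-protocol result.

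**Preferred.** Make primary an analysis of all randomised women in the arm allocated. Use a baseline-adjusted longitudinal model on the month-12 and month-24 scans, with treatment, visit, their interaction and baseline, and name month 24 as the main contrast. State the missing-data assumption (such a model takes data as missing at random). Ask women who stop the spray to attend the scans already scheduled. Keep per-protocol as the supportive estimate of effect under adherence, with membership fixed before unblinding.

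**Cost.** Enrolment stays at 100 and no visit is added; the work is in wording, follow-up effort and a little more analysis. The ITT effect may be smaller than under full adherence, with the loss of power shown in step 5 of the working. Women with no follow-up scan remain missing, so their number by arm should be reported and the missing-data assumption tested.

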**Methods:**

One hundred postmenopausal women will be included in a randomized, placebo-controlled, double-blind trial comparing the effect of nasal salmon calcitonin (200 UI/day) to placebo over two years. Bone microarchitecture at the distal radius and distal tibia will be determined yearly by high-resolution peripheral quantitative computerized tomography (p-QCT) with a voxel size of 82 μm and an irradiation of less than 5 μSv. Serum markers of bone resorption and bone formation will be measured every 6 months. Safety and compliance will be assessed. Primary endpoint is the change in bone microarchitecture; secondary endpoint is the change in markers of bone turnover.

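### The efficacy ANCOVA makes no joint use of the interim scans and marker samples, so the month 24 estimate is biased if drop-out follows interim results, and some precision is lost

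*Protocol article*

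**What the plan says.** The Statistical analysis section sets out the efficacy model in full: "The change from baseline between the two different groups (active treatment/placebo) will be compared by an analysis of covariance (ANCOVA) model", a "model with change as the response variable, the baseline value as a covariate, and treatment as a fixed factor". It also states: "For each analyzed parameter a two-sided t-test will be applied". Neither method has a term for visit or for the correlation between repeated values in the same woman.

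The primary efficacy analysis "will be based on the observed data of the per-protocol population". The intention-to-treat analysis is optional: "Secondarily, an ITT analysis may be performed to test the robustness of the results". The same section calls the trial exploratory ("the primary analysis of the efficacy endpoints in this exploratory trial").

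The data are longitudinal. For the scans: "Bone microarchitecture will be investigated by p-QCT at baseline and after one and two years". For the markers, the abstract says: "Serum markers of bone resorption and bone formation will be measured every 6 months". Table 2 confirms p-QCT at baseline, month 12 and month 24, and markers at screening, baseline and months 6, 12, 18 and 24. The End points section speaks of change over the two years and names no visit. The Sample size calculation section expects 20% drop-out, hence 100 enrolled for 80 evaluable.

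**The concern.** A model with one change value per woman can take one visit, or one summary, at a time. When it is applied to month 24, a woman who left after her month 12 scan is absent, although that scan says something about where she was heading. The same holds for the markers, which have three interim samples before month 24.

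Two things follow. First, if women leave in relation to their on-treatment results, those still present at month 24 are a selected group, and nothing in the model corrects for it. If the selection differs between arms, the treatment difference is shifted. Second, information already collected goes unused, which costs some precision. At stake is the size, and possibly the detection, of the effect that this proof-of-concept trial is meant to show.

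**Working it through.** **Inputs from the documents.** Difference of 3.5% in BV/TV, 80% power, 40 per arm, 20% drop-out and 100 enrolled (Sample size calculation); visit times (Table 2); model and analysis set (Statistical analysis).

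**Assumed, because the documents do not give them.** Two-sided alpha of 0.05; the SD of change; the correlation ρ between month 12 and month 24 change, given baseline and treatment (0.3 to 0.9); the timing and mechanism of drop-out.

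**1. The plan's own figure.** 80 / (1 − 0.20) = 100, which reproduces. The 80 cannot be checked without an SD. Solved backwards, SD = 3.5 / [(1.960 + 0.842) × √(2/40)] = 3.5 / 0.626 = 5.59 (5.52 with the t distribution). It serves below only as a scale.

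**2. Precision at month 24.** When women who leave have a month 12 value, the variance of a joint-model estimate relative to ANCOVA on completers is

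1 − ρ² × (1 − n24/n12),

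with n24 = 40 per arm. If every drop-out has a month 12 scan, n12 = 50; if half do, n12 = 45. For ρ = 0.7 and n12 = 50: 1 − 0.49 × 0.20 = 0.902, and √0.902 = 0.950, so the standard error is 5.0% lower.

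| ρ | SE lower, n12 = 50 | Power | SE lower, n12 = 45 | Power |
|---|---|---|---|---|
| 0.3 | 0.9% | 80.7% | 0.5% | 80.4% |
| 0.5 | 2.5% | 82.0% | 1.4% | 81.1% |
| 0.7 | 5.0% | 83.9% | 2.8% | 82.2% |
| 0.9 | 8.5% | 86.4% | 4.6% | 83.6% |

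If no drop-out has a month 12 scan (n12 = 40), or nobody drops out, the gain is zero. On simulated complete data the two estimates were identical. This was worked out for the scans only. The markers have more interim visits, but for a month 24 contrast their gain also comes only from drop-outs.

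**3. Bias at month 24.** 4,000 simulated trials, 50 per arm, true difference 3.5, SD 5.59, ρ = 0.7, correlation of baseline with change −0.3, about 20% leaving after month 12. Where leaving depends on a value, the log-odds slope is 1.2 per SD; for month 12 change, worse change makes leaving more likely.

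| Drop-out depends on | ANCOVA, completers | Joint model |
|---|---|---|
| nothing (random) | 3.49 | 3.49 |
| baseline | 3.48 | 3.48 |
| baseline, opposite directions by arm | 3.50 | 3.49 |
| month 12 change, both arms | 3.34 | 3.50 |
| month 12 change, placebo arm only | 2.45 | 3.52 |

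Simulation error is about 1.19/√4000 = 0.02, so the first three rows show no bias. In the last row 10% of the active arm leaves at random. With 20.8% leaving overall, placebo drop-out is 2 × 20.8 − 10 = 31.6%.

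**4. What this means.** Shared mechanism: 3.50 − 3.34 = 0.16, or 0.16/5.59 = 0.03 SD. Placebo-only mechanism: 3.50 − 2.45 = 1.05, or 0.19 SD, which is 30% of the effect. With the planning standard error 5.59 × √(2/40) = 1.25, a mean of 2.45 gives power Φ(2.45/1.25 − 1.96) = Φ(0) = 50%, against the planned 80%.

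**The case against.** The strongest reply is that baseline-adjusted ANCOVA is a standard, valid model for an exploratory trial, and that the large bias comes from a chosen scenario. Patients and staff are blinded, the common side effects described are nasal, and no rule in the article ties scan results to withdrawal. When both arms share the mechanism the bias is 0.03 SD. Even the placebo-only bias of 1.05 is below one standard error (1.18 in that simulation). This stands as a limit on size. It does not make arm-specific drop-out implausible: DXA is repeated at month 12 in women admitted with T-scores down to −2.49, and a woman whose result worsens may leave, more often on placebo if the drug works. That route is an inference, not something the article states.

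A second reply also stands in part. If the per-protocol set excludes drop-outs (its definition is not shown), a repeated-measures model fitted to that set gains little. The model and the analysis set must therefore change together.

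A reader might infer more than the documents support:

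- **That the ANCOVA needs drop-out to be completely at random.** It does not. It conditions on baseline and treatment and stays unbiased when leaving depends on these, as the second and third rows of the simulation table show.
- **That the plan analyses one visit and discards month 12, or tests each marker four times.** No visit is named. ANCOVAs at each visit, or on a summary of visits, also fit the text. The choice of visit may lie in an analysis plan that is not shown, and its absence here is no finding.
- **That repeated measures bring a large precision gain for the markers.** A large gain comes from averaging over visits. That answers a different question, and an ANCOVA on the average would achieve it too.

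**Conclusion.** The point holds in a limited form. The stated model makes no joint use of the interim scans and samples. With 20% drop-out its month 24 estimate is biased if leaving depends on interim on-treatment results: slightly if both arms share the mechanism (3.34 for a true 3.5), substantially if one arm alone has it (2.45). It is not biased if leaving depends only on baseline or treatment. The precision that a joint model would recover is 0 to 8.5% of the standard error, or up to about 6 points of power, and nothing with complete data.

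These sizes rest on the assumed SD, alpha, correlation and drop-out mechanisms. In an exploratory trial this is a worthwhile improvement of moderate to low weight, not a defect that invalidates the design.

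**What to change.** For the p-QCT parameters and for P1NP and CTX, replace the stated ANCOVA by a mixed model for repeated measures on change from baseline. Its terms are treatment, visit, treatment-by-visit, baseline and baseline-by-visit, with unstructured covariance. Fit it to all randomized women with at least one post-baseline value, and name the month 24 contrast as the main p-QCT result. State that the model assumes data missing at random given the observed values; it does not protect against leaving that depends on values never seen. The per-protocol ANCOVA can stay as a supporting analysis.

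Averaging the marker effect over months 6 to 24 is an option. If it is wanted, it should be declared as a different estimand, not presented as a gain in efficiency.

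The cost is revised wording and slightly more analysis work in standard software. No visits, scans, samples or participants are added, and with complete data the month 24 estimate equals that of the ANCOVA.
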